### Procedure for unblinding if needed {17b}

Throughout the study, there will be no permission to reveal the allocation to either the outcome assessor or the patients. However, once the study is completed, the patients will be informed about their group allocation.

## Data collection and management

### Plans for assessment and collection of outcomes {18a}

Outcomes are assessed at two time points, at baseline, and after treatment sessions, by the blinded examiner who has enough experience and knowledge to do it. Also, the demographic data will be gathered by the examiner in the first session. The Persian version of the CFQ-R questionnaire used for quality of life assessment has been validated by Talebi et al. and the Cronbach-alpha for the CFQ-R was 0.65–0.91 for children and parents’ version, and ≥ 0.70 for the adult version, showing good internal consistency [43, 44]. The questionnaire forms can be accessed through the Supplementary file 3.

### Plans to promote participant retention and complete follow-up {18b}

Participant retention and complete follow-up are promoted by the monitoring of the physical therapist. In case of withdrawal of patients from the study, their data will be counted as drop-outs.

### Data management {19}

Throughout all stages of the trial, utmost care will be taken to ensure the security and confidentiality of participants’ personal information. All participant data, including reports, data collection, process details, and administrative forms, will be stored in lockable file cabinets located in restricted-access areas. These documents will be identified solely by a coded ID number, maintaining anonymity. Instead of using names, the participant’s unique number identifier will be utilized in all data records. Forms, lists, logbooks, appointment books, and any other materials connecting participant ID numbers to identifiable information will be kept in a closed, separate file within a restricted zone. Only the primary investigator will have knowledge of the participants’ names associated with their respective numbers. To enhance data management, all collected data will be converted into electronic format and securely stored in password-protected files at the main study centers where the data originated. Access to this data will be strictly limited to the research team. Personal data will be stored separately from other information, treated as highly confidential, and accessible only to specifically authorized research team members. It will not be shared with any external parties, ensuring its complete privacy.

### Confidentiality {27}

The data of all patients will be stored and archived in a strictly confidential manner throughout all stages of the trial. The confidentiality of the data will be safeguarded not only during the trial but also after its completion.

### Plans for collection, laboratory evaluation, and storage of biological specimens for genetic or molecular analysis in this trial/future use {33}

Respiratory sputum samples will be obtained for the sputum culture test in the hospital’s laboratory. Patients will be provided with enough information about the test and sampling methods in the informed consent form (Supplemental file 1) alongside other information provided. There is no intention to do other analyses on these samples in this study; however, if they are used in future research, they will be reported and published as “secondary data analysis.”

## Statistical methods

### Statistical methods for primary and secondary outcomes {20a}

Data will be analyzed using Stata version 16. The normal distribution of data will be analyzed by the Shapiro–Wilk test. If the distribution is normal, parametric tests will be used for analysis before and after the intervention. To determine the homogeneity of variances (i.e., variances approximately equal across groups), Levene’s test will be employed. If the variance is equal, the analysis of covariance (ANCOVA) will be used. The covariance variable in this test will be the initial data values before the intervention. The significance level of the tests is set at 0.05. In addition to the significance index, the effect size index is also used by Cohen’s *d* method to compare two treatment methods for each variable. Therefore, the effect of the intervention on each of the dependent variables is determined, regardless of the sample size. According to the new interpretation presented, the effect size can be divided and interpreted as follows: from 0.01 to 0.2, very small; from 0.2 to 0.5, small; from 0.5 to 0.8, moderate; from 0.8 to 1.2, large; from 1.2 to 2, very large; and more than 2, very large [46].

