CPT is still the standard and most widely used method for children and adolescents with CF, because teaching other ACT methods has proven to be difficult for them to follow, and their effectiveness depends on correct learning and implementation processes. However, due to the inconvenience, time-consumption, and dependence of CPT on others, nowadays it is not uncommon, for most patients and even their families to prefer the alternative methods [7]. Also, aerobic exercise is a readily available activity that is practicable and clinically recommended [20].

Several studies have investigated the effectiveness and quality of the implementation of unsupervised interventions at home by patients or their parents [9, 29, 30], with results demonstrating that treatment adherence is 30% [9]. Study results reveal that unsupervised treatment has fewer positive effects compared with supervised treatment [25, 31, 32]. Numerous studies, including systematic reviews (alluding to the controversy in the results of aerobic exercises and the low methodological quality of these studies), have mentioned the need for further investigation in this field so that it can be credible to recommend the possibility of using aerobic exercises as a viable alternative and independent ACT [17, 20, 33–35].

To the best of the authors’ knowledge, a study comparing aerobic exercise with CPT with high-quality and precise design has not yet been investigated. Therefore, this study aims to compare the effect of aerobic exercises compared to CPT on pulmonary function, functional capacity, sputum culture, and quality of life in patients with CF. This is so that if significant changes are observed due to aerobic exercises compared to CPT, clinically, aerobic exercises can be recommended among treatment priorities.

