### Objectives and hypotheses {7}

In this trial, we aim to include 30 children and adolescents of CF patients into a 1:1 randomized controlled trial study. We will compare the effects of conventional chest physiotherapy (CPT) and sham aerobic exercise in one group and aerobic exercise and sham CPT in the other group. The primary objective is to evaluate the effects of the 18-session aforementioned treatments on pulmonary function (FEV1) and functional capacity in children and adolescents with CF. The secondary objective is to assess the changes in sputum culture, pulmonary function (FVC), and quality of life of CF patients.

We hypothesize that there will be an increase by at least 7.1% in FEV1% percent predicted (minimally clinical important difference (MCID) considered for FEV1 [36]), a significant increase in the amount of FVC, at least 33-m increase in the distance covered in 6MWT (MCID considered for 6MWT [36]), a significant increase in the percentage of negative sputum culture tests and reduction of colony count tests after 6 weeks of aerobic exercise and CPT in CF patients, and a significant difference between the two groups. Also, the CFQ-R quality of life questionnaire score is expected to have a significant increase of at least 11.4 points in the physical domain, 7.3 points in the respiratory domain (MCIDs considered for CFQ-R [36]), and in the overall score.

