### Trial design {8}

The current project is a double-blind 1:1 randomized controlled trial study designed to investigate and compare the effects of aerobic exercises and CPT in two parallel groups: group A consisting of CPT plus sham aerobic exercise and group B consisting of aerobic exercise and sham CPT. This study will be conducted at the CF specialized clinic of the Children’s Medical Center Hospital, Tehran, Iran; children and adolescents with confirmed diagnoses of CF will be randomly allocated to either group A or B.

Primary data points including FEV1, 6MWT, and secondary outcomes including sputum culture test (key secondary), FVC, and CFQ-R quality of life questionnaire will be assessed before and after treatments. It is expected that both treatments will have meaningful effects on the aforementioned variables and if significant changes are observed due to aerobic exercises compared to CPT, clinically, aerobic exercises will be recommended among treatment priorities.

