### Criteria for discontinuing or modifying allocated interventions {11b}

The medical recommendations of individuals, such as drug treatments and airway clearance methods, will not be changed. Due to the risk of cross-infection, two infected patients will not be in the same environment at the same time [3]. Participants are asked to use their 7% sodium chloride nebulizer at home before their treatment session, to prepare the airways [39].

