### Relevant concomitant care permitted or prohibited during the trial {11d}

Before the treatment starts, the ACBT technique, one of the main ACTs proven to be effective and safe [11], will be thoroughly taught to the patients and their parents and a guidance paper will be given to them. One week before the treatment starts, patients are asked to replace their sports activities with ACBT. Also, they are asked to do the technique on the days between their treatment days, twice a day, at home. The ACBT implementation is checked by the conductor every session. The steps to implement the technique are breathing control, chest expansion, and forced expiration technique (FET) [11].

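### Before-after gains within an arm cannot show that either treatment works; only the randomised, baseline-adjusted difference between arms can carry the conclusions

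*Protocol article*

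**What the plan says.** Objectives and hypotheses {7} makes two separate kinds of statement. The first is about change from baseline: "We hypothesize that there will be an increase by at least 7.1% in FEV1% percent predicted" and "at least 33-m increase in the distance covered in 6MWT", both figures being the cited MCIDs. The second is comparative. The two are joined in one sentence: "after 6 weeks of aerobic exercise and CPT in CF patients, and a significant difference between the two groups". Trial design {8} repeats the first kind: "It is expected that both treatments will have meaningful effects on the aforementioned variables".

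Statistical methods {20a} states that, if the data are normal, "parametric tests will be used for analysis before and after the intervention". It then plans Levene's test, ANCOVA with the baseline value as covariate, and Cohen's d to compare the two treatments.

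The design has two arms, CPT with sham exercise and exercise with sham CPT (Trial design {8}). Outcomes are measured at baseline and at 6 weeks only (Outcomes {12}).

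On shared care, section {11d} has ACBT taught to all patients. It continues: "One week before the treatment starts, patients are asked to replace their sports activities with ACBT". It also asks for ACBT twice a day at home on the days between sessions. Section {11b} asks for nebulised 7% saline before each session, and says that individual medical recommendations, "such as drug treatments and airway clearance methods, will not be changed".

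**The concern.** Randomisation protects only the contrast between the arms. The change from baseline in one arm is an uncontrolled before-after comparison, and no untreated or double-sham arm shows what would have happened without either treatment. If paired tests are reported beside the ANCOVA, two conclusions become available that the design cannot support. One is that both treatments work, because both arms improved. The other is that one works and the other does not, because only one arm's p-value fell below 0.05. The hypotheses invite the first, since they predict a gain of at least one MCID after both treatments in addition to a difference between them.

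**Working it through.** **1. The plan's own figure.** Sample size {14} starts from 11 per arm in an earlier trial and adds 30%: 11 × 1.3 = 14.3, rounded up to 15 per arm, 30 in total. This reproduces the stated number. (Dividing by 1 − 0.30 gives 15.7, so 16 per arm.) The stated power of 0.8 cannot be reproduced, because no effect size or SD is given. Nothing below depends on it.

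**2. What each quantity estimates.** Let τA and τB be the specific effects of the two regimens. Let g be everything the arms share: home ACBT, stopping sports, saline, practice on spirometry and the walk test, regression to the mean, and time.

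- Expected change in arm A: τA + g
- Expected change in arm B: τB + g
- Difference between arms: (τA + g) − (τB + g) = τA − τB

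With two active arms and two time points, g cannot be separated from τA or τB. It cancels only in the between-arm difference.

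**3. How often a within-arm test misleads.** The SDs and gains here are assumptions, since the protocol gives none, and the 7.1 is read as points of % predicted. Set τA = τB = 0, with 15 per arm and two-sided α = 0.05. The power of a paired t-test in one arm comes from the noncentral t distribution with 14 df and noncentrality (g/SD) × √15. For g = 3.5 and SD = 8 this is 0.4375 × 3.873 = 1.69, giving 35%.

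| Shared FEV1 gain g | SD 6 | SD 8 | SD 10 |
|---|---|---|---|
| 0 | 5% | 5% | 5% |
| 2 | 23% | 15% | 11% |
| 3.5 | 56% | 35% | 24% |
| 5 | 85% | 62% | 44% |
| 7.1 | 99% | 89% | 73% |

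For 6MWT with an assumed change SD of 45 m, shared gains of 10, 20 and 33 m give 12%, 36% and 75%. At 33 m the range is 98% to 51% for SDs of 30 to 60 m.

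**4. Both arms together.** This is a simulation of 10,000 trials with FEV1 change SD 8, baseline mean 75 and SD 18 (all assumed), and no effect of either treatment. The fourth column is the second minus the third.

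| g | At least one arm significant | Both | Exactly one | ANCOVA between arms |
|---|---|---|---|---|
| 0 | 9.2% | 0.2% | 9.0% | 4.6% |
| 3.5 | 58.6% | 12.2% | 46.3% | 5.2% |
| 5 | 84.9% | 37.8% | 47.1% | 5.1% |
| 7.1 | 98.6% | 79.6% | 19.1% | 4.8% |

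At a shared gain of 3.5 to 5 points, nearly half of such trials would show one arm significant and the other not, although the two treatments are identical by construction. The ANCOVA holds its 5% error rate throughout.

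**5. Size of the shared exposure.** Three sessions a week leave at most 4 days for ACBT: 4 × 2 × 6 = 48 home ACBT sessions at most, against 3 × 6 = 18 supervised sessions. This counts exposure; it does not measure bias.

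**The case against.** The strongest reply is that the plan is already comparative. Every method named in {20a} after the quoted sentence compares the arms, and that sentence could mean tests on data collected at the two time points. The Abstract, Trial design {8} and the Discussion tie the clinical recommendation to a difference between the treatments. Much of this stands. A reader might infer that the plan tests each arm formally against the MCID, but {20a} names no paired test and no MCID. A reader might also infer that the main comparison is compromised. It is not, because the shared care cancels there.

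Four other readings go further than the text:

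- **All children are new to ACBT.** This is not established. The history of airway clearance is recorded at baseline (Other variables), so some may already use it. ACBT replaces sports from one week before treatment, and the first session follows the first examination by 30 minutes ({11a}). Part of its effect may therefore already be in the baseline.
- **Sections {11b} and {11d} flatly contradict each other.** They are in tension as written, but compatible if ACBT is an addition to unchanged individual care. The text does not say so.
- **The trial fails its own aim because both arms receive ACBT.** The phrase "using aerobic exercises as a viable alternative and independent ACT" describes what earlier studies and reviews say needs investigating. This trial's stated aim is a comparison with CPT.
- **A null result will be reported as equivalence.** The protocol does not say that of this trial. How wide the between-arm interval will be is a question of precision, separate from this one.

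What the reply does not remove is the wording of {7} and {8}. The gains after treatment are hypothesised in their own right, beside the between-group difference, and before-after testing is the natural way to examine them. This is stated text, not detail left to an analysis plan.

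**Conclusion.** The point holds in a limited form. Before-after gains in this trial cannot show that CPT or aerobic exercise works, whatever their size or p-value, because nothing in the design separates treatment from what the arms share. That conclusion rests on the design alone. The percentages illustrate how often a within-arm test could mislead (35% to 89% in a given arm for shared gains of 3.5 to 7.1 points at SD 8) and depend on assumed SDs, assumed gains and 15 completers per arm. With 11 completers the same range is 26% to 76%. That within-arm tests are planned is an inference from the wording, though the most natural one. The randomised ANCOVA and the comparative decision rule are sound on this point. What is at risk is the set of additional claims the report could make.

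**What to change.** 1. In {20a}, name the baseline-adjusted between-arm difference, with its 95% CI set against 7.1 points for FEV1 % predicted and 33 m for 6MWT, as the only confirmatory result.
2. Report before-after changes within arms descriptively (mean change with its spread), without significance tests.
3. In {7}, drop the gains of at least one MCID after each treatment as tested hypotheses. They may stay as background expectations. Edit {8} to match.
4. Word the conclusions as a comparison of the two regimens given on top of home ACBT, as {11d} now stands.
5. Reconcile {11b} and {11d}, so that the reader can tell how the ACBT given to all children relates to the individual airway clearance that is to stay unchanged.

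The cost is wording only: no new data, visits or patients. Since recruitment has started, the change should be registered as an amendment before the allocation codes are broken.

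### The primary baseline-adjusted ANCOVA is made conditional on Shapiro–Wilk and Levene pre-tests that are uninformative at 15 per arm, and Cohen's d is wrongly said to determine the effect whatever the sample size

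*Protocol article*

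**What the plan says.** The section on statistical methods for primary and secondary outcomes {20a} sets out a sequence:

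- A normality check: "The normal distribution of data will be analyzed by the Shapiro–Wilk test".
- Its consequence: "If the distribution is normal, parametric tests will be used for analysis before and after the intervention".
- A variance check: "variances approximately equal across groups), Levene’s test will be employed".
- Its consequence: "If the variance is equal, the analysis of covariance (ANCOVA) will be used".
- The covariate: "The covariance variable in this test will be the initial data values before the intervention".
- The level: "The significance level of the tests is set at 0.05".

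The same section adds that "the effect size index is also used by Cohen’s *d* method to compare two treatment methods for each variable". It draws the conclusion that "the effect of the intervention on each of the dependent variables is determined, regardless of the sample size" and then lists fixed size bands for d, with cut-points at 0.01, 0.2, 0.5, 0.8, 1.2 and 2.

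This section governs both primary outcomes. The Sample size section {14} plans 15 patients per arm. The Objectives section {7} and the Outcomes section {12} adopt minimal important differences of 7.1% for FEV1 % predicted and 33 m for the walk test.

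**The concern.** ANCOVA is itself a parametric test, so the two conditional sentences together mean that both pre-tests must pass before the named primary model is used. Three things are wrong with that rule.

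- The confirmatory model depends on significance tests of the trial's own outcome data, at a sample size where those tests reject sound data by chance and miss real departures.
- The section speaks of data and never of residuals. The normality assumption in ANCOVA concerns residuals. In patients aged 6 to 18, walk distance and FEV1 in litres vary with growth, so non-normal values would not by themselves show that the model is unsuitable.
- A failed pre-test may move the analysis away from the model that uses baseline, and so lose precision that a 30-patient trial can hardly spare.

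The sentence on Cohen's d is a second, smaller fault. The value of d does not grow with the sample size as a test statistic does, but its precision depends on the sample size. A size label without an interval would over-read the result.

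**Working it through.** **Inputs.** From the protocol article: 15 per arm, 1:1 allocation, α = 0.05 (two-sided assumed) and baseline as covariate. The 15 is reproduced from the Sample size section: 11 × 1.3 = 14.3, rounded up to 15. The article gives no SDs, no distributions and no pre-post correlation. The shapes below, and the correlation of 0.7 where one is needed, are therefore assumptions.

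**1. How often the pre-tests reject sound data.** Simulated trials with normal, equal-variance outcomes, 15 per arm, each test at 0.05. The article does not say how the tests are applied, so several readings were run:

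| Shapiro–Wilk applied | Levene centring | Both pass | ANCOVA turned away |
|---|---|---|---|
| Pooled over arms | median | 92% | 8% |
| Pooled over arms | mean | 91% | 9% |
| Per arm | median | 87% | 13% |
| Per arm | mean | 86% | 14% |
| Per arm and time point (four tests) | mean, post values | 77% | 23% |

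The range is 8% to 23% per outcome, although every assumption holds.

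**2. How often they miss real departures (15 per arm).** Levene's test detects a true SD ratio of 1.5 in about 27% of trials and a ratio of 2 in about 60% to 62%. Shapiro–Wilk rejects a moderately skewed sample (lognormal, log-SD 0.5) in about 39%. A pass is therefore weak evidence that the assumption holds.

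**3. Type I error.** This needs an assumed fallback; a Mann–Whitney test on change scores was used (6,000 runs per case):

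| Null case | Two-stage rule | ANCOVA always |
|---|---|---|
| Normal, equal SD | 0.047 | 0.047 |
| SD ratio 1.5 | 0.049 | 0.051 |
| SD ratio 2 | 0.056 | 0.057 |
| Lognormal, log-SD 0.5 | 0.044 | 0.041 |

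A separate set of null runs gave 0.046 to 0.055 for the two-stage rule.

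**4. Power.** Here the assumed fallback is a rank test that ignores baseline, with a true shift of 0.8 SD (on the log scale for the skewed case). Power falls from 83% with ANCOVA always to 79% under the two-stage rule for normal data, and from 76% to 61% for skewed data. A rank test on change scores, which keeps the baseline information, showed little or no loss when checked. The cost therefore depends on the fallback.

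**5. Precision of Cohen's d.** With n per arm, t = d·√(n/2) on 2n − 2 degrees of freedom. The 95% limits are the noncentrality parameters that place t at the 97.5th and 2.5th percentiles, divided by √(n/2).

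- For d = 0.5 and n = 15: t = 0.5 × √7.5 = 1.37 on 28 df, which gives -0.23 to 1.22.
- Check by normal approximation: SE = √(2/15 + 0.25/60) = √0.1375 = 0.371, and 0.5 ± 1.96 × 0.371 gives -0.23 to 1.23.
- For d = 0.5 and n = 11: -0.36 to 1.34.
- For d = 0.5 and n = 150, for contrast: 0.27 to 0.73.

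The interval at 15 per arm starts below zero, covers the very small, small, moderate and large bands, and just enters the band that begins at 1.2. With no true effect, the chance of |d| ≥ 0.5 is 2·P(T ≥ 1.37 on 28 df) = 18% at 15 per arm.

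**The case against.** The best defence has four parts.

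**A fallback may exist elsewhere.** A reader might infer that a failed pre-test leaves the trial with no analysis at all, in 14% of outcomes or, for two primaries, in 1 − 0.857² = 27% of trials (0.857 being the unrounded 86% pass rate in the working). The documents do not support that. A fallback is the kind of detail an article leaves to a full protocol or analysis plan, and neither is shown. The section on additional analyses {20b} does say that the methods are given in the text, but that does not prove a fuller document is silent. The 27% also treats two outcomes from the same patients as independent. This part of the defence stands. It does not rescue the two-stage rule, because a stated fallback would complete that rule without making the pre-tests informative.

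**The error rate holds.** A reader might infer that choosing the test after seeing the data breaks the 0.05 level. The simulations do not show this. The largest departure found was 0.077, for ANCOVA among only those trials that passed the pre-tests at an SD ratio of 2. That is a conditional rate, under a variance imbalance the article gives no sign of. The overall rate stayed near 0.05. This part also stands.

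**Data need not mean raw values.** The article does not say so literally. It is the plain reading, since residuals are never mentioned, but it remains a reading.

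**Cohen's d only supplements the test.** A reader might infer that d is meant to settle the effect in place of the test. The article introduces it as an addition to the significance result. The authors may have meant only that d does not scale with n as a p-value does, which is fair. The sentence as written claims more.

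**Conclusion.** The point holds in a limited form. The article fixes its primary analysis badly by making a sound model depend on pre-tests that, at 15 per arm, turn it away in about 8% to 23% of outcomes when nothing is wrong and miss an SD ratio of 1.5 about 73% of the time (100% − 27%). The likely harm is lost power and an avoidable dependence of the method on the data, not a demonstrated breach of the 0.05 level. The 8% to 23% range rests on normal data and on how the tests are applied. The power loss rests further on an assumed fallback that ignores baseline. The sentence on Cohen's d is wrong as written, whatever those assumptions: at this size one estimate is compatible with most of the plan's own bands and with an effect in the opposite direction. This should be corrected, but it does not undermine the design, because baseline-adjusted ANCOVA is a good choice.

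**What to change.** In section {20a}:

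1. State baseline-adjusted ANCOVA as the primary analysis of FEV1 % predicted and 6-minute walk distance, without conditions.
2. Remove Shapiro–Wilk and Levene as preconditions, and examine the residuals of the fitted model instead.
3. Name one robust or permutation version of the same model as a sensitivity analysis. HC3 standard errors are one option. They were slightly conservative at this size (null rejection 0.032 to 0.043 in simulation), with a small loss of power. Which version to use is a matter of preference.
4. Report the adjusted between-arm difference with its 95% CI, in % predicted and in metres, beside the 7.1% and 33 m thresholds the plan already adopts.
5. Give any standardised effect with its 95% CI, and delete the phrase claiming independence from sample size.

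The cost is wording only. No patient, visit or measurement changes. Because recruitment is stated to have begun in July 2023, make and date the change before any comparison of outcomes by arm, through the amendment route the article describes.

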### Sample size {14}

The prevalence of CF disease is lower in the Asian continent [1] as reported as 1 per 100,000–350,000 in the Middle East and 1 per 100,000 in Iran [5]. Thus, the number of diagnosed CF patients is low. On the other hand, the coordinating center has dedicated the CF specialized clinic of the Children’s Medical Center Hospital to the trial team, for a limited short time frame. Considering these factors, we selected the randomized controlled trial study by Sosa et al. [45] which was closest to our trial in terms of methodology and variables, as the basis for sample size calculation. In this study, 22 participants, 11 in each group, were recruited. Adding a 30% drop-out rate probability to each group, we anticipate recruiting 15 participants in each trial arm. Using power analysis, the required sample size with a power of 0.8 and an α of 0.05, a total sample size of 30 children and adolescents is determined.

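### The effect size the protocol names, Cohen's d, is not tied to the baseline-adjusted ANCOVA, so at 15 per arm its size label can misdescribe the effect that was tested

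*Protocol article*

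**What the plan says.** Section {20a} of the protocol article makes the between-group test conditional on normality and variance checks: "If the variance is equal, the analysis of covariance (ANCOVA) will be used". Baseline adjustment belongs to that test: "The covariance variable in this test will be the initial data values before the intervention". The threshold follows: "The significance level of the tests is set at 0.05".

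The effect size comes next and is introduced as an addition to the test: "In addition to the significance index, the effect size index is also used by" Cohen's d, as a "method to compare two treatment methods for each variable. Therefore, the effect of the intervention on each of the dependent variables is determined". The section says this holds whatever the sample size, and then gives labels for reading d, beginning "from 0.01 to 0.2, very small; from 0.2 to 0.5, small; from 0.5 to 0.8, moderate; from 0.8 to 1.2, large".

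The section does not say whether d is built from week-6 means, change scores or ANCOVA-adjusted means, or which SD is the denominator. It names no adjusted mean difference and no confidence interval. Elsewhere, the objectives {7} and outcomes {12} state clinical relevance in natural units: 7.1% for FEV1 and 33 m for the 6MWT.

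**The concern.** The p-value and the labelled effect size may describe two different contrasts. The ANCOVA compares the arms after allowing for baseline. Cohen's d as usually computed is the difference of two group means over their pooled SD, with no baseline term. FEV1 and 6-minute walk distance after six weeks can be expected to depend strongly on where the child started. Ages run from 6 to 18, only FEV1 below 30% is excluded for severity, and section {16a} names no stratification factor. In a trial of 30, a chance baseline gap of some size is therefore likely.

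At stake is the label that readers will quote. A moderate d could be reported where the adjusted effect is near zero, or a trivial d beside an adjusted effect that matters. Neither figure can be set against the 7.1% or 33 m thresholds.

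**Working it through.** **Inputs from the protocol article.** Arm size ({14}): 11 × 1.3 = 14.3, rounded up to 15 per arm, which reproduces the stated total of 30. Covariate, alpha of 0.05 and size bands are from {20a}; the FEV1 threshold of 7.1 points is from {12}.

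**Assumptions, since the document gives no figures.** Correlation r between baseline and week 6 of 0.7, 0.8 or 0.9; equal SDs; normal data; two-sided test; SD of FEV1% predicted of 20, so that one MCID is 7.1 / 20 = 0.355 SD.

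**Step 1: the two quantities.**
- Default d = (difference in week-6 means) / pooled SD.
- Adjusted difference = (difference in week-6 means) − b × (difference in baseline means), where b is the ANCOVA slope.
- With equal SDs, b is about r. So default d ≈ adjusted d + r × g, where g is the baseline gap in SD units.

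**Step 2: size of the chance gap.** SD of g = √(2/15) = 0.365. P(|g| > 0.3) = P(|Z| > 0.82) = 41%. P(|g| > 0.5) = P(|Z| > 1.37) = 17%.

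**Step 3: one example.** Adjusted d = 0.3 (small), g = −0.4, r = 0.8: default d ≈ 0.3 + 0.8 × (−0.4) = −0.02. With r = 0.7 it is 0.02, and with r = 0.9 it is −0.06.

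**Step 4: no true effect.** Default |d| ≥ 0.5 means |t| ≥ 0.5 × √(15/2) = 1.37 on 28 df, which has probability 18% whatever r is. The adjusted value has an approximate SD of 0.365 × √(1 − r²) = 0.26, 0.22 and 0.16 for the three correlations, so it reaches 0.5 far less often. Simulation gives the exact rates.

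**Step 5: simulation.** 40,000 trials per setting, 15 per arm. Default d on week-6 values is compared with the ANCOVA-adjusted difference over the pooled baseline SD.

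| | r = 0.7 | r = 0.8 | r = 0.9 |
|---|---|---|---|
| No true effect: default d at least 0.5 in size | 18% | 18% | 18% |
| No true effect: adjusted d at least 0.5 in size | 7% | 3% | 0.5% |
| No true effect: opposite signs | 25% | 30% | 36% |
| True 0.355 SD: different size band | 55% | 59% | 63% |
| True 0.355 SD: opposite sign and ANCOVA p < 0.05, of all trials | 0.2% | 1% | 5% |
| True 0.355 SD: among significant trials, default d below 0.2 or reversed | 5.5% | 11% | 22% |

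**Step 6: sensitivity to what the text leaves open.**
- Change-score d over the baseline SD: with no true effect it reaches 0.5 in 9%, 4% and 0.5% of trials, close to the adjusted value. At 0.355 SD its sign differs from the ANCOVA in at most about 6%, and almost never when p < 0.05.
- Change-score d over the SD of the changes: the band differs from that of the adjusted value in 48%, 62% and 89%, because the denominator differs.
- Adjusted difference over the ANCOVA residual SD: a true 0.5 on the pooled-SD scale becomes a median of 0.71, 0.84 and 1.16, which runs from moderate to large.
- 11 completers per arm: default and adjusted d differ by more than 0.2 in about 33% to 61% of trials for r from 0.5 to 0.9, against 27% to 55% with 15.

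**The case against.** The strongest reply is that a reader might infer a planned unadjusted d, and the text does not say that. The d sentence follows closely on the ANCOVA sentences, and a d from adjusted means is compatible with the wording. This stands: the week-6 form is the usual default, and taking it as the plan is an inference. What is left is still more than a detail for an analysis plan to settle. The article itself chose d, gave it bands and the role of determining the effect, and section {20b} says the methods for the outcomes are set out in the text. Step 6 shows that the label depends on which form is used.

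Second, d is supplementary. The trial design {8} and the discussion tie clinical priority to a significant difference, and no decision is attached to a band. This also stands, so the conclusion concerns what is reported and not the decision rule.

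Third, a reader might infer that d will often point the opposite way to a significant ANCOVA. The figures do not support that. The 25% to 36% sign disagreement arises when both estimates scatter around zero; with a significant ANCOVA, reversal stays at or below about 1% of all trials unless r is near 0.9.

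Finally, default d is not shifted by randomised baseline gaps on average: at r = 0.8 and a true 0.5 its median is 0.50, as for the adjusted value. The trouble is extra noise, and error in the one trial that happens to have a gap.

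**Conclusion.** The point holds as one of specification and size. The protocol pairs a baseline-adjusted test with an effect-size measure that has no stated link to it, no stated means and no stated SD. If d takes its default form, its label differs from that of the adjusted effect in about 55% to 63% of trials at a true effect of 0.355 SD. With no true effect, it reaches 0.5 in about 18% of trials against 0.5% to 7%. These figures rest on the assumed correlations of 0.7 to 0.9 and, for the 0.355, on an SD of 20. They would be smaller with a lower correlation and would change with a change-score d.

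The point covers the continuous outcomes only. Neither ANCOVA nor Cohen's d fits the positive/negative and graded sputum culture results, and the ANCOVA applies only where the preliminary checks pass. It does not depend on the sample-size justification. It should be corrected, but it does not undermine the planned test.

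**What to change.** Replace the Cohen's d sentence in {20a} with wording such as: for each continuous outcome, the effect estimate is the baseline-adjusted mean difference from the ANCOVA with its 95% confidence interval, in the units of the outcome; any standardised value is this adjusted difference divided by a named SD, for example the pooled baseline SD.

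The estimate then has the same sign as the test and can be read against 7.1% and 33 m. The choice of SD is a convention; what matters is that it is named beforehand. The cost is one sentence: the baseline values are already collected, the model is already planned, and the sample size is unchanged.
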